## 3.2 Sample Size and Estimated Duration of Study

A total of 30 volunteers will be vaccinated in 2 cohorts of 15 (see **Section 9.1.4** for a justification of the sample size). Twelve in each cohort will be randomized to receive 10 or 40 µg of MSP2-C1 formulated in ISA720; 3 in each cohort will be randomized to receive ISA720 Control. The trial is expected to last for a total of 56 weeks. Each volunteer will be followed for 48 weeks from the time of the first injection.

It is estimated that up to 150 volunteers will need to be screened to complete enrolment.

## 3.3 Group Allocation, Randomisation and Blinding

The two dose groups will be screened and enrolled consecutively. Once screening has started and the first 15 participants have been deemed eligible, they will be assigned to Cohort 1 and a Day 0 visit will be scheduled. Alternates may also be identified and held in reserve. The first dose group will be vaccinated over the course of 1-2 days, with 2 participants completed a day prior to the remaining 13. If the alternates are not vaccinated, they will be invited to participate as members of the second cohort. The second dose cohort will be split into 2 subgroups for vaccination. The first 5 participants of the 40 µg dose cohort will be vaccinated at least 4 weeks after the last vaccination of the previous dose cohort and the remaining 10 participants in this dose cohort will be vaccinated at least 4 weeks after the first 4 participants in their cohort to maximize safety. After the first vaccination for each dose cohort, no replacement volunteers will be added if a subject withdraws from the study.

In this trial, everyone will be blinded to the randomisation scheme except for the study pharmacist (or designee) who prepares the vaccine dose for administration. Randomization and blinding occur within each dose cohort. The study pharmacist/nominee will prepare identical syringes containing the study vaccines, according to a randomisation schedule provided by the study statistician, so that personnel who perform the study assessments do not know the identity of the study vaccine. Each participant considered eligible for vaccination will be assigned a randomisation number at Visit 1 (Day 0) (Section 6.4). The randomization number will used to identify the participant throughout the remainder of the study.

The volume of vaccine and ISA720 Control will be identical for each group. The study pharmacist will provide the person administering vaccine with the subject’s randomisation number, initials, and a blinded syringe containing the study medication. The pharmacist (or designee) will not inform any of the investigational staff of the treatment assignment and will not perform any other subject-related duties.

The Sponsor will provide the Investigator with code-break envelopes for individual participants. These should be retained intact and returned to the Sponsor with the completed Case Report Forms (CRFs) at the end of the study, unless the Investigator needs to break the code for an individual subject. Code-break envelopes for all participants will also be held by the sponsor and may be broken for an individual subject(s) or for the entire study at the request of the SMC to evaluate serious adverse events. The code for a subject should only be broken in exceptional circumstances, e.g. in the case of a medical emergency or where the Investigator feels that knowledge of the subject’s treatment will aid his/her management of the event. In the latter case, approval of the sponsor should be obtained whenever possible. Any code break should be documented in the study file, including a rationale for the break.

Allocation of the study subjects will not be disclosed to the scientists undertaking the exploratory immunological studies (anti-MSP2 antibody by ELISA, and CMI responses) until these test results are completed for each cohort. The GIA and IFA require unblinding and this can be done following the anti-MSP2 antibody assay completion.

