Thirty volunteers will be enrolled and assigned to one of two dose groups (10 or 40µg) or ISA720 Control as outlined in **Table 1**. All vaccines and the ISA720 Control will contain the same amount of Montanide® ISA720. As with other recombinant protein vaccines, hypersensitivity reactions would be expected to occur within the first 24 hours after receipt of the vaccine, and other severe local or systemic reactions within 72 hours. As outlined above, delayed local reactions have been observed in previous ISA720 vaccine studies. Thus, volunteers will be reviewed on days 3, 7, 14 and 28 following each vaccination, and vaccinations will be staggered within the higher dose cohort such that 5 volunteers will be vaccinated 4 weeks prior to the remaining 10 volunteers. Stopping rules as detailed in **Section 7.5** below will be in place to enable suspending the trial until review by the safety monitoring committee (SMC).

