## 6.4 Clinical Monitoring and Evaluation

The following sections provide a detailed listing of the procedures and studies to be performed in this protocol at designated time points. See **Appendix 1** for a tabular representation of study procedures. In addition to the procedures listed below, photographs of the injection site may be taken at baseline and/or on follow-up visits to better assess local reactogenicity.

Study Day 0 **(FIRST VACCINATION, visit 1)**

1. Verify that all applicable eligibility criteria have been met.
2. For females, obtain a urine sample for -hCG testing. Ensure that test is negative before vaccinating; a positive test will exclude the volunteer from the trial.
3. Verify that Study Participation Informed Consent was obtained and a copy of this provided to the subject.
4. Medical Investigator to perform medical history and physical examination, to assess eligibility to enter vaccine phase.
5. Record vital signs (blood pressure, temperature, heart rate, and respiratory rate).
6. Obtain approximately 24 mL of blood for hematology (FBC and differential), biochemistry (electrolytes creatinine, liver function tests, CPK), and blood for study of humoral immune response by anti-MSP2 ELISA.
7. Administer the vaccine, and record which arm utilised.
8. Observe for at least 30 minutes after vaccination to evaluate for immediate adverse reactions. Vital signs will be repeated prior to leaving the clinic.
9. Education by study staff during 30-minute post-immunisation wait period describing proper use of digital thermometers, injection-site reaction measurement, and vaccine side-effect diaries. Study staff will also discuss signs and symptoms of potential AEs.
10. Distribute Days 0-6 diary card.
11. Record adverse events and concomitant medications.

Study Day 1 (Phone Call ONLY)

1. Phone call to inquire about diary card entries and injection site reactions since last visit.

Study Day 3 (visit 2)

1. Study staff to perform targeted history and examine injection site, emphasising examination of any acute complaints, with review by the medical investigator if required.
2. Record vital signs.
3. Obtain approximately 9 mL of blood for haematology (FBC and differential), and biochemistry (creatinine, liver function tests).
4. Record adverse events and concomitant medications.

Study Day 7 +/- 1 (visit 3)

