## 7.5 Criteria for Placing the Study on Hold

If a dose of vaccine is considered significantly reactogenic (see below), additional vaccinations will be suspended until a thorough review by the independent Medical Monitor and SMC and discussion between the Principal Investigators, the Medical Monitors, and Sponsors. Resumption of vaccinations will start only if all parties agree to a resumption of vaccination. The communications from the SMC will subsequently be forwarded by the investigators to the respective IRBs.

The following criteria will be used to define significant reactogenicity:

1. One or more volunteers experience an SAE (as defined in **Section 7.1.2** in this protocol) that is determined to be possibly, probably, or definitely related to the vaccine (as defined in **Section 7.2.3** in this protocol), **OR**
2. One or more volunteers experience anaphylaxis that is probably or definitely related to the vaccine, **OR**
3. Occurrence of any severe clinical illness in one or more volunteers that is not explained by another diagnosis unrelated to vaccination, **OR**
4. Two or more volunteers experience a Grade 2 or higher laboratory abnormality, with the exception of CPK. In the case of CPK, if in the absence of other explanation (vigorous unaccustomed exercise) one volunteer experiences a Grade 3 or higher elevation of CPK or if two or more volunteers experience a Grade 2 elevation of CPK.
5. One volunteer experiences a Grade 3 clinical AE that is determined to be probably or definitely related to the vaccine, with the exception of isolated Grade 3 local erythema or swelling.
6. The principal investigator (PI) may, using discretion, ask for the study to be placed on hold and an SMC meeting to be held for any single event or combination of multiple events which, in professional opinion, jeopardize the safety of the participants or the reliability of the data.

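### After the Day 0 observation, nothing requires the two cohort 1 lead volunteers to be reviewed before the other 13 get their first dose

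*Protocol*

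**What the plan says.** Section 3.3 sets the order of first doses in cohort 1 (10 µg): "The first dose group will be vaccinated over the course of 1-2 days, with 2 participants completed a day prior to the remaining 13". It gives no purpose for the lead and no condition for going on to the 13.

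Section 3.1 expects hypersensitivity within 24 hours and "other severe local or systemic reactions within 72 hours". It places its explicit within-cohort stagger (5, then 10 four weeks later) in the higher-dose cohort only.

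Section 6.4 sets what happens to each volunteer after the injection:

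- Day 0: "Observe for at least 30 minutes after vaccination to evaluate for immediate adverse reactions", with vital signs repeated before the volunteer leaves.
- Day 1: "Study Day 1 (Phone Call ONLY)", asking about diary entries and injection-site reactions.
- Day 3: "Study Day 3 (visit 2)", with the first scheduled injection-site examination and blood tests after the dose.

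Under Section 7.5, if a dose proves significantly reactogenic, "additional vaccinations will be suspended until a thorough review by the independent Medical Monitor and SMC". One trigger, item 5, is "One volunteer experiences a Grade 3 clinical AE that is determined to be probably or definitely related to the vaccine". Redness or swelling at the injection site that reaches Grade 3 on its own is exempt from it. The first scheduled SMC meeting in Table 1 is at week 11.

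**The concern.** A lead pair protects the volunteers behind it only if what is seen in the pair can stop the next injections. Section 2.3.2 says this combination formulation has not been given to humans before, so a lead pair is sensible. As written, though, the 13 may be injected on Day 1 without anyone having asked how the two leads are.

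A Section 7.5 hold can stop only injections not yet given. Suppose a lead develops Grade 3 injection-site pain at 48 hours. Section 7.2.3 treats every injection-site reaction as causally related, and the exemption in item 5 covers isolated erythema or swelling, not pain. A hold would be expected, but no first dose in cohort 1 would be left to withhold.

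The stake is confined to those 13 first doses. Second and third doses, and all of cohort 2, come weeks later and stay protected by the hold rules.

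**Working it through.** **Timing.** The protocol gives no calculated figure here, so this is interval arithmetic.

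- Lead: one day, about 24 hours (3.3).
- Hypersensitivity window: 24 hours (3.1). Shortfall 24 − 24 = 0, so it is covered.
- Window for other severe reactions: 72 hours (3.1). Shortfall 72 − 24 = 48 hours.
- First scheduled examination after Day 0: Day 3 (6.4), which is 3 − 1 = 2 days after the 13 are injected.
- Day 1 call: the same day as the 13 injections, with neither order nor decision stated.

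A lead of one day also needs two vaccination days, so a span that may be as short as one day does not fit the rest of the sentence.

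**Allocation of the pair.** Cohort 1 is 12 vaccine and 3 control (3.2). Assume no separate randomisation block for the pair.

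- Both on vaccine: (12 × 11)/(15 × 14) = 0.629
- Exactly one: (2 × 12 × 3)/(15 × 14) = 0.343
- Neither: (3 × 2)/(15 × 14) = 0.029

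**Chance of a severe local reaction in a vaccinated lead, at any time.** Section 2.3.3 offers two rates: 1% cumulative for intramuscular ISA720 vaccines, and one severe reaction after the first dose among 10 + 10 + 9 = 29 volunteers in the AMA1/ISA720 trial (1/29 = 0.0345).

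- Both leads on vaccine: 1 − 0.99² = 0.0199, and 1 − (28/29)² = 0.0678.
- Averaged over allocation: 0.6286 × 0.0199 + 0.3429 × 0.01 = 0.0159, and 0.6286 × 0.0678 + 0.3429 × 0.0345 = 0.0544.

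**Within the uncovered interval.** What matters is onset between the end of Day 1 dosing and 72 hours. The protocol gives no onset times. Purely as an assumption, take 25% to 75% of these reactions to begin then:

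- At the 1% rate: 0.0159 × 0.25 = 0.0040 to 0.0159 × 0.75 = 0.0119.
- At 1/29: 0.0544 × 0.25 = 0.0136 to 0.0544 × 0.75 = 0.0408.

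That is 0.4% to 4.1% overall. The chance of a hold trigger is lower again, because isolated Grade 3 erythema or swelling is exempt. Severe systemic reactions are left out, since no rate is given for them.

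**If it happens.** With at least one lead on vaccine, 12 − 2 = 10 or 12 − 1 = 11 of the 13 have already received vaccine.

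**The case against.** The strongest reply is that nothing here is inconsistent. A reader might infer that Section 3.1 requires a 72-hour lead and that Section 3.3 breaks this. The text does not support that. Section 3.1 draws two consequences from its windows, the follow-up visits and the stagger in the higher-dose cohort, and promises nothing for cohort 1. One day matches the hypersensitivity window, and putting the long stagger at the higher dose is defensible. This stands.

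The background risk is also low. ISA720 has been given to more than 450 subjects with no SAEs reported. Recombinant 3D7 MSP2 has been given with it in the Combination B trials, and cohort 1 receives 10 µg in total, against 3 × 4 = 12 µg in the lowest-dose group of those dose-comparison trials. This stands too, although that experience covers the 3D7 form and not this formulation.

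The probabilities are soft. The 1/29 rests on one event, the 1% covers whole vaccination courses and not just first doses, and the onset share is assumed. Two blinded leads, at least one of them on control with probability 0.343 + 0.029 = 0.371 (unrounded), carry limited information. A 72-hour lead would still miss the delayed reactions, which began 10 days or later.

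Finally, safeguards exist: the Day 1 call, the diary, a clinician on call at all hours and the investigator's discretionary hold. A reaction reported early on Day 1 could stop some or all of the 13. That is true, but it depends on the volunteer reporting in time or the call happening to come first. None of these is a required check.

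**Conclusion.** The point holds as a gap in sequencing, of low severity. The lead exists, but no step makes its findings count before the other 13 injections.

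The chance that this matters is small: about 1.6% to 5.4% for a severe local reaction at any time in a vaccinated lead, and less in the uncovered interval by a share the protocol does not give. These figures assume that the pair is drawn at random from the 12:3 allocation, that the Section 2.3.3 rates carry over to this vaccine, and that severe there means roughly Grade 3 here.

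A reader might go further and conclude that cohort 1 dosing is unsafe or that nothing could stop the 13. Neither follows. The Day 1 call and the hold rules are real, and an event known before an injection can prevent it. The case for change is that an existing contact can be made a working check at almost no cost. How long the lead should be is more a matter of judgement.

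**What to change.** In Section 3.3, change the one-to-two-day span to at least 2 days and add: 'None of the remaining 13 will be vaccinated until the Day 1 contact with both lead participants has been completed and checked against Section 7.5.' This reorders steps already scheduled and adds no visit and no day.

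Preferably, vaccinate the 13 at least 72 hours after the pair, once the clinical findings of the pair's existing Day 3 visit have been checked against Section 7.5. The cost is about two days, once, for 13 first injections and for cohort 2, which is timed from cohort 1, in a 56-week trial. The note to Table 1 already treats the vaccination times as minimums and allows first vaccinations to be delayed. Waiting for the Day 3 laboratory results as well would add their turnaround time, which is not stated; the proposal does not require it.

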## 6.2 Screening (Up to 28 Days Prior to Vaccination)

1. Explain the study via the Participation Informed Consent (Appendix 6) and gain Screening Informed Consent (Appendix 5) from the volunteer.
2. Ensure the subject has signed the Screening Informed Consent and received a signed copy.
3. Elicit a complete medical history, including menstrual and contraceptive history and/or history of surgical sterility for female participants. Counsel females of childbearing potential to utilize effective contraception during the study.
4. Elicit a social history including smoking and alcohol use
5. Undertake a complete physical examination.
6. Counsel females of childbearing potential to utilize effective contraception during the study.
7. Obtain approximately 19 mL of blood for hematology, biochemistry, serologic tests for viral hepatitis B and C and HIV in all volunteers and an extra 10 mL blood for -HCG testing in females. Pre- and post-test counseling for blood borne viruses will take place as per existing SOP.
8. Obtain 45 ml blood for PBMC for CMI and serum for CMI assay for CMI immunity testing and for humoral immunity studies (anti-MSP2) by GIA and IFA. NB Sample can be collected Study Day 0 Pre-vaccination depending on laboratory availability.
9. Urine collection for dipstick testing.
10. Verify inclusion/exclusion criteria.
11. A screening number will be assigned to each volunteer.

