### 6.7.1.2 Immunofluorescence microscopy

A selection of samples that were found to be positive to MSP2 by ELISA will be tested for reactivity to the surface of merozoites using confocal immunofluorescence microscopy. *In vitro* cultures of *P. falciparum*-infected erythrocytes at the schizont stage will be smeared on glass slides, fixed, and probed with ELISA-positive serum from vaccinnees and from recipients of ISA720 Control.

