### Growth Inhibition Assay

The GIA is designed to determine whether anti-MSP2 antibodies obtained from a vaccinee can inhibit merozoite invasion of red cells. This will be performed using two different established approaches, in [name]’s laboratory, NIH (MVI-supported GIA Reference Center), and [name]’s Laboratory, WEHI (34).

Synchronized mature blood-stage parasites from the 3D7 and FC27 lines are incubated with purified IgG ([name] Laboratory) or dialysed serum ([name] Laboratory) from volunteer sera *in vitro*. The number of infected red cells will be determined by assaying parasite lactate dehydrogenase activity ([name] Laboratory) or by flow cytometry ([name] Laboratory). Growth inhibitory activity is defined as the percentage reduction in the number of newly invaded red cells (determined by parasitemia) by post vaccination serum/IgG compared to serum/purified IgG from Day 0 samples or samples from recipients of the ISA720 Control. In addition to 3D7 and FC27, serum samples may also be tested against parasites expressing MSP2 with other sequences

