Graphs will display growth inhibition expressed as a percent of inhibition comparing test sera to pre-immune sera. Depending on the distribution of the data, parametric or non-parametric methods will be used to compare inhibition as a function of dose, and serotype.

Should the need arise for terminating the study early, the investigative team will discuss with the SMC the reason for termination and determine which study questions can be addressed in an unbiased manner with the available data. The available data will be analyzed and interpreted in light of early termination. Deviations from the statistical plan will be reported in the study report.

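### Section 3.3 unblinds the GIA and IFA without giving a reason or limiting who is unblinded, although allocation is needed only to select and label Control sera

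*Protocol*

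**What the plan says.** Section 3.3 sets a general rule: "everyone will be blinded to the randomisation scheme except for the study pharmacist (or designee) who prepares the vaccine dose for administration". It explains that syringes are prepared so that those who assess subjects do not know which product was given.

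For the laboratories it continues: "Allocation of the study subjects will not be disclosed to the scientists undertaking the exploratory immunological studies (anti-MSP2 antibody by ELISA, and CMI responses"), and this holds "until these test results are completed for each cohort". The next sentence makes the exception: "The GIA and IFA require unblinding and this can be done following the anti-MSP2 antibody assay completion".

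The assay descriptions and the analysis section add:

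- **GIA reference, section 6.7.3:** inhibition by post-vaccination serum or IgG is "compared to serum/purified IgG from Day 0 samples or samples from recipients of the ISA720 Control".
- **GIA reference, section 9.1.3.1:** "Graphs will display growth inhibition expressed as a percent of inhibition comparing test sera to pre-immune sera".
- **IFA, section 6.7.1.2:** the test material is "A selection of samples that were found to be positive to MSP2 by ELISA", with serum from vaccinees and from Control recipients, examined by confocal microscopy.
- **Baseline sample, section 6.2:** pre-vaccination blood is drawn "for humoral immunity studies (anti-MSP2) by GIA and IFA", at screening or on Day 0 before the injection.

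**The concern.** The exception is a fixed statement in the protocol, not a detail left to the statistical analysis plan. It departs from the general rule and from the treatment of ELISA and CMI two lines above, and it has no stated limit.

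GIA and IFA carry the functional evidence: whether vaccine-induced antibody inhibits parasite growth and recognises MSP2 on the merozoite surface. Section 2.1 reports that rabbit antibodies to these same antigens did not inhibit invasion, so any apparent inhibition in humans would attract attention. Someone who knows allocation can influence which sera are tested, how a fluorescence image is read, which runs are repeated and, where two references are allowed, which one is used. The likely direction favours a vaccine effect.

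**Working it through.** The protocol gives no figure to reproduce here. The check is to ask, task by task, what allocation is needed for.

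1. **GIA against pre-vaccination serum (section 9.1.3.1).** Appendix 1 schedules GIA samples at screening and on Days 112, 196 and 336. Pairing a later sample with the baseline one needs subject number and visit. Allocation is not needed.
2. **GIA against Control recipients (the alternative in section 6.7.3).** Someone must know which sera are Control. That is a labelling step. The assay can be run on coded samples and the comparison made afterwards.
3. **IFA (section 6.7.1.2).** This assay is not defined against the subject's own baseline. The panel needs ELISA-positive vaccinee sera and Control sera, so someone must know allocation to assemble it. Preparing and reading the slides does not require it.
4. **Western blots (section 6.7.2).** These also use selected positive sera and Control sera, yet section 3.3 does not mention them. Under section 6.7 one laboratory (WEHI) performs ELISA, immunofluorescence, blots and one of the two GIAs, so unblinding it for GIA or IFA would expose the blots too.
5. **Consistency of the GIA reference.** Section 6.7.3 allows Day 0 samples or Control samples and does not say that the Day 0 sample is the subject's own. Section 9.1.3.1 names only pre-immune sera, and only for the graphs. The choice is open at the point where allocation becomes known.

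**Extent.** Section 3.2 gives 3 Controls in each of 2 cohorts: 3 × 2 = 6. With four scheduled GIA time points there are at most 30 × 4 = 120 scheduled samples, of which 6 × 4 = 24 come from Controls. Only a selection goes to IFA, by a rule that is not stated.

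**Delay if release waits for both cohorts.** Table 1 puts last visits at week 48 for cohort 1 and week 56 for the last of cohort 2: 56 − 48 = 8 weeks. The timings in Table 1 are minimums, so this is a lower figure.

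**The case against.** Several points on the other side stand.

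- **Some unblinding has a purpose.** Control sera cannot be identified without allocation. A reader might infer that the unblinding brings no benefit; steps 2 and 3 of the working show otherwise.
- **Unblinded reading is not stated.** A reader might infer that the laboratories choose the sera, repeat runs and read results with allocation known. The wording is passive and would also fit unblinding of a sample list alone. Unblinded running and reading is a fair inference from the contrast with ELISA and CMI, no more.
- **ELISA results already reveal much.** Volunteers are malaria-naive and the Control contains no antigen, so a laboratory holding the ELISA results can guess allocation. This argues for new codes, not for open disclosure.
- **GIA leaves little to judgement.** It is read by lactate dehydrogenase activity or flow cytometry and is mainly summarised descriptively. Section 9 specifies no IFA analysis.
- **Dose is not hidden in any case.** Section 9.1.3.1 foresees comparing inhibition by dose and serotype, but the dose groups are consecutive cohorts blinded only within dose. Blinding to allocation would not conceal 10 versus 40 µg.
- **The primary objective is safety.** A reader might infer a threat to the safety assessment. The last ELISA sample is taken on Day 336, the final visit. If completion means all time points of a cohort, its scheduled follow-up has ended before unblinding.

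**Conclusion.** The point holds in a limited form. The protocol declares that GIA and IFA need unblinding, gives no reason and sets no limit on who is unblinded, although allocation is needed only to select and label Control sera. The two statements of the GIA reference also differ and should be made one.

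The size is modest and cannot be quantified from the document. The risk concerns active versus Control within a cohort, where few Controls make a small number of influenced readings visible. The conclusion assumes that the exception is meant to reach the people who run or read the assays. If only a sample list is meant, the defect is one of wording, and the same sentence cures it. The change is worth making because the bias is avoidable at little cost. It casts no doubt on the primary safety objective.

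**What to change.** Replace the sentence in section 3.3 with:

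> *An unblinded person not involved in the assays (for example the study statistician) selects the active and Control sera and supplies them under new codes that cannot be linked to the ELISA results. GIA, IFA and Western blots are run and read blind, and allocation is released to the laboratories only after those results are locked.*

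The pharmacist should not take this role, because section 3.3 bars the pharmacist from further duties concerning subjects. The person chosen should be named as an exception to the general blinding rule.

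In sections 6.7.3 and 9.1.3.1 use one GIA reference, the subject's own pre-vaccination sample, and report Control recipients as a separate group. Saying pre-vaccination rather than Day 0 matches section 6.2, which allows collection at screening. The blots keep the sera that section 6.7.2 already plans; no pre-immune samples need be added.

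The cost is one coded sample list with relabelled aliquots. If release waits for both cohorts, cohort 1 waits about 8 weeks. No extra assays are required.
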